## Abstract

**Background::**

To our knowledge, only 1 study has investigated the effects of kinesio taping (KT) on pulmonary function and functional capacity of patients with chronic obstructive pulmonary disease (COPD). Therefore, there is still a lack of high-quality evidence to prove the effectiveness of KT for COPD patients. Our purpose was to investigate the effect of KT on respiratory function and muscle strength in the COPD patients who were in stable condition.

**Methods::**

This research project has been received ethical approval from the Medical Research and Ethics Committee in Affiliated Nanhua Hospital, University of South China. This work is a part of a comprehensive research project to assess and provide intervention that potentially improves respiratory function and quality of life among patients with COPD. Participants recruited into the study need to fulfill the following criteria: clinical diagnosis of COPD and symptoms indicative of exacerbation; spontaneous breathing on hospital admission; and physiotherapy since the first day of hospitalization. Patients will be assigned at random to the COPD medical treatment + KT (Group 1), or the COPD medical treatment alone (Group 2). The outcome measures are pulmonary function and respiratory muscle strength. The level of statistical significance is set as *P* < .05.

**Results::**

This protocol will provide a reliable theoretical basis for the following research.

**Conclusions::**

It was hypothesized that thoracic KT could significantly change pulmonary function and functional capacity in patients with COPD.

**Trial registration::**

This study protocol was registered in Research Registry (researchregistry6632).

## Introduction

1

Chronic obstructive pulmonary disease (COPD) is a chronic inflammatory disorder caused by the inhalation of tobacco smoke or other irritants. It is characterized by progressive deterioration in pulmonary function and persistent airway inflammation. Its symptoms include difficulty in breathing, coughing, mucus (sputum) production, and wheezing.^[1]^ Patients with COPD usually exhibit an upper chest breathing pattern and dyspnea on exertion. The disease also presents extrapulmonary manifestations such as skeletal muscle dysfunction, which is an important prognostic factor that justifies exercise intolerance in these patients.^[2]^

Several treatment strategies for COPD are provided in the current literature, which includes limited bed rest, pharmacological therapy, Oxygen therapy, and physiotherapy. Physiotherapy interventions, such as breathing exercises and early mobilization, aim to restore or maintain muscle function during an acute episode of COPD.^[3–5]^ Physical therapists often use these strategies to relieve dyspnea, improve thoracoabdominal coordination, and enhance functional capacity in patients with COPD exacerbations.^[6]^

A relatively new treatment method for COPD is kinesio taping (KT), which is being widely used as a relatively novel band-aid method to reduce the pain of musculoskeletal disorders. KT is an elastic bonding material containing high tensile capacity, which ensures the free movement of the application area without the need of drugs or chemicals. KT can be extended to 140% of the original length, providing a good range of motion in comparison with other types of tape.^[7,8]^ Studies have shown that KT improves blood and lymph circulation, mitigates pain, adjusts joints, and relives muscle tension. Although the effect of KT on pain is unclear, KT may provide afferent stimuli that promote pain inhibition mechanisms and pain relief.^[9,10]^ Depending on the proposed effects, we speculated that if KT were applied to thorax, it could have some beneficial effects to restore respiratory muscle function and to reduce hyperinflation, thereby resulting in increased functional capacity for patients with COPD.

To our knowledge, only 1 study has investigated the effects of KT on pulmonary function and functional capacity of patients with COPD.^[11]^ Therefore, there is still a lack of high-quality evidence to prove the effectiveness of KT for COPD patients. In this study, our purpose was to investigate the effect of KT on respiratory function and muscle strength in the COPD patients who were in stable condition. It was hypothesized that thoracic KT could significantly change pulmonary function and functional capacity in patients with COPD.

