### Population

2.2

Participants recruited into the study need to fulfill the following criteria: clinical diagnosis of COPD and symptoms indicative of exacerbation; spontaneous breathing on hospital admission; and physiotherapy since the first day of hospitalization. The exclusion criteria are as follows: patients who are uncooperative, those have previous thoracic surgery, thoracic deformities or any condition that make it difficult to apply the KT, and those with reports of allergic skin reactions to the use of adhesive bandages, plasters, or other adhesive materials.

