### Intervention protocol

2.4

In Group 1, KinesioTex Gold is used for KT application. Patients are seated on a chair. When the patients are at the end of the expiration, it will be applied bilaterally on the fifth to sixth and ninth to tenth intercostal muscles transversally and on the anterior and posterior axillary line longitudinally with 50% tension. To stimulate the muscle and support the function, the stimulation technique is usually applied from the origin to the insertion of the muscle with the recommended stretching of 25 to 50%. KT is changed on every fifth day (for a total of 3 times and 15 days) by the same certified physiatrist who has previously attended the KT training course. The patients are instructed not to take the tapes off at any time but they are allowed to take showers. The researcher, who is blind to the type of treatment, completes posttreatment (15th day) evaluations for each patient and recorded the data.

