## Discussion

3

The purpose of medical treatment of COPD is to reduce the frequency and severity of the symptoms and to improve the functional capacity and the quality of life. To our knowledge, only 1 study has investigated the effects of KT on pulmonary function and functional capacity of patients with COPD. Therefore, there is still a lack of high-quality evidence to prove the effectiveness of KT for COPD patients. In this study, our purpose was to investigate the effect of KT on respiratory function and muscle strength in the COPD patients who were in stable condition. It was hypothesized that thoracic KT could significantly change pulmonary function and functional capacity in patients with COPD. In our protocol, a total of 120 subjects will be recruited.

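### The objective names COPD patients in stable condition, but the mandatory inclusion criteria admit only hospitalised patients with exacerbation symptoms, and nothing reconciles the two

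*Protocol article*

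**What the plan says.** **Objective.** The Introduction ends with the statement that "our purpose was to investigate the effect of KT on respiratory function and muscle strength in the COPD patients who were in stable condition". The Abstract's Background gives the same target, and the Discussion again places the purpose "in the COPD patients who were in stable condition".

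**Eligibility.** Section 2.2 (Population) opens with "Participants recruited into the study need to fulfill the following criteria" and then lists "clinical diagnosis of COPD and symptoms indicative of exacerbation; spontaneous breathing on hospital admission; and physiotherapy since the first day of hospitalization". The Abstract's Methods carries the same list. The exclusions in section 2.2 cover "patients who are uncooperative, those have previous thoracic surgery, thoracic deformities or any condition that make it difficult to apply the KT", and also known skin reactions to adhesives.

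**Hypothesis.** In the Abstract's Conclusions, the Introduction and the Discussion, the hypothesis refers to patients with COPD in general, without the word 'stable'.

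**Size.** The Discussion gives a planned total of 120 subjects.

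**The concern.** The population is part of the trial question. Here it is described in two ways that pull in opposite directions: a stable phase of the disease in the objective, and a hospital admission with exacerbation symptoms in the criteria. Each description is repeated, so neither can be dismissed as one slip of the pen.

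What is at stake is the conclusion. A site that follows section 2.2 recruits inpatients with exacerbation symptoms. A reader who takes the objective from the Abstract, Introduction or Discussion will read the result as evidence about stable COPD. The effect would then be credited to patients whom the criteria did not admit.

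**Working it through.** No arithmetic applies and the plan gives no figure to reproduce. The check sets the statements side by side.

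| Element | Where | What it requires or names |
|---|---|---|
| Objective | Abstract (Background), Introduction, Discussion | COPD, stable condition |
| Inclusion | Abstract (Methods), section 2.2 | COPD, exacerbation symptoms, hospital admission with spontaneous breathing, physiotherapy from the first hospital day |
| Exclusion | Section 2.2 | Cooperation, chest surgery or deformity, obstacles to taping, adhesive reactions |
| Hypothesis | Abstract (Conclusions), Introduction, Discussion | COPD, no phase named |

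1. *Are the inclusion criteria optional?* No. Section 2.2 says that participants need to meet them, and the items form one list joined by 'and'. A COPD patient without exacerbation symptoms, or one who has not been admitted, is not eligible.
2. *Do the exclusions bring the sample back towards the objective?* No. None removes patients in an exacerbation and none demands stability.
3. *Does any other text bridge the gap?* The article does not define stability, require patients to have stabilised before randomisation, or plan a stable subgroup. Section 2.3 mentions a baseline examination but does not place it in time relative to admission.
4. *How many participants are affected?* Since the criteria bind everyone, all of the planned 120 subjects enter with exacerbation symptoms. This restates the contradiction and is not a separate estimate of harm.
5. *Does the mismatch reach the randomised comparison?* Write the change from baseline to day 15 as R + T with taping and R without it, where R is the average change that would occur anyway and T is the taping effect. The difference between arms is (R + T) − R = T. Random allocation makes R the same in expectation in both arms, so it cancels. T is then the effect in the patients enrolled, that is, inpatients with exacerbation symptoms.

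Steps 1 to 4 establish the contradiction. Step 5 limits its consequence to the population for which T may be claimed.

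**The case against.** **'Stable' may mean stabilised during the admission.** This is the most favourable reading, and since the word is never defined it cannot be ruled out outright. A condensed article may also leave the timing of baseline to the full protocol, so that silence is not itself a fault. But the article does not state this reading, and a requirement of physiotherapy from the first hospital day points towards acute inpatients. Even if it is what the sponsor meant, the text would still lead two readers to enrol different patients. The objection tempers how firmly one may call the populations mutually exclusive. It does not remove the contradiction.

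**The hypothesis does not say 'stable'.** This is correct. The randomised comparison can address a hypothesis about COPD in general, at least for the kind of patient enrolled. It follows that a reader who infers that the trial cannot answer its own question goes too far. That holds only for the question about stable COPD as the objective words it.

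**Recovery from the exacerbation.** The article has a blinded researcher who "completes posttreatment (15th day) evaluations for each patient", and a reader might infer that recovery during those 15 days biases the trial's result. The documents do not support that. There is a concurrent randomised control arm (section 2.3) and a between-group test (section 2.6), and recovery common to both arms cancels there. A change within one arm cannot be attributed to taping alone, but that is a separate matter about within-group tests, and correcting the population wording would not cure it. The documents also give no figure for the size of such recovery.

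**Conclusion.** The point holds as an internal contradiction between the objective and the eligibility criteria, and it must be resolved because it determines for whom the result may be claimed. It affects every participant recruited under the criteria as written. It carries no estimate of bias, and internal validity is not in question on this ground.

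The conclusion rests on the ordinary meaning of the two descriptions, since 'stable' is undefined, and on the criteria being applied as mandatory, as section 2.2 says. The documents do not settle which population the sponsor intends, so this review does not presume it.

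**What to change.** Reconcile the objective in the Abstract (Background), Introduction and Discussion with the criteria in the Abstract (Methods) and section 2.2, before enrolment. There are two routes, and the sponsor has to say which population is meant.

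- **If the criteria stand:** reword the objective to patients hospitalised with COPD exacerbation symptoms. Limit the hypothesis and conclusions in the Abstract (Conclusions), Introduction and Discussion to the same population. There the edit adds the population; there is no 'stable' wording to remove from the hypothesis. This is a text change with no additional patients or procedures. The cost is a narrower claim.
- **If stable COPD is intended:** change the eligibility criteria in both places. This is more than wording, because it alters who is recruited and in what setting.

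The registry entry is not among the documents, so whether it also needs amending cannot be judged here. The sponsor should check it against the chosen population.

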## Materials and methods

2

### Ethical approval

2.1

This work is a part of a comprehensive research project to assess and provide intervention that potentially improves respiratory function and quality of life among patients with COPD. This research project has been registered in the research registry (with number: researchregistry6632) and received ethical approval from the Medical Research and Ethics Committee in Affiliated Nanhua Hospital, University of South China (no. Tzey3208523). After the introductory briefing, the acceptance to take the presession questionnaire implied the participant's consent to participate in the study.

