### Random and blind

2.3

Before starting the study, a randomization list is produced using software-generated randomized numbers; the randomization depends on random blocks of 10. Patients will not know to which group they are assigned or which treatment they will be offered. Patients will be assigned at random to the COPD medical treatment + KT (Group 1), or the COPD medical treatment alone (Group 2). Participants are enrolled by the research assistant. After baseline examination, all patients will be given a full explanation of the treatment protocol and will be required to sign a written informed consent for study participation and for publication of the results. All the data collectors, doctors, statistical analysts, as well as result assessors are not aware of grouping assignment (Fig. 1).

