### Outcome measure

2.5

The outcome measures are pulmonary function and respiratory muscle strength. Pulmonary function was measured using a spirometer. To perform the measurement, subjects were instructed to sit on an armless chair with back support while their knees flexed to 90° and nostrils occluded by a nose clip. Then they performed a maximal inspiration followed by a forced expiration, exhaling as much air as possible 3 seconds. This maneuver was repeated 3 times, and the highest scores were recorded for analyses. Respiratory muscle strength will be measured as maximum inspiratory pressure (MIP) and maximum expiratory pressure (MEP), using an analogic manovacuometer. The assessments are performed in accordance with American Thoracic Society/European Respiratory Society standards (2002). The participants are assessed in the seated position. The MIP maneuver begins near residual volume, and the MEP maneuver begins near total lung capacity. The maximum score of 3 maneuvers varying by less than 20% will be recorded.

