### Statistical analysis

2.6

All analyses will be performed using SPSS for Windows, version 16, and GraphPad InStat. Analysis of variance is used for comparing mean values of patient's age, weight, height, and body mass index. For nonparametric measures, differences between baseline and posttreatment scores for each group are computed by the Wilcoxon signed ranks test. The difference between each treatment group is performed by the Kruskal–Wallis test. The level of statistical significance is set as *P* < .05.

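### Sections 2.1 and 2.3 give conflicting rules for consent to the study, and 2.3 places the full explanation and signature after the baseline examination

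*Protocol article*

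**What the plan says.** Section 2.1 (Ethical approval) reports ethics approval and then gives a consent rule. Once the introductory briefing is over, "the acceptance to take the presession questionnaire implied" the patient's consent to take part in the study. It mentions no signature.

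Section 2.3 (Random and blind) gives a different rule: "After baseline examination, all patients will be given a full explanation of the treatment protocol", and the same patients "will be required to sign a written informed consent for study participation and for publication of the results".

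Two further places bear on what the baseline examination is for. Section 2.5 states: "The outcome measures are pulmonary function and respiratory muscle strength". It measures the first by spirometer and the second as MIP and MEP. Section 2.6, for measures it calls nonparametric, states: "differences between baseline and posttreatment scores for each group are computed by the Wilcoxon signed ranks test".

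The Discussion gives the planned total as 120 subjects.

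**The concern.** Consent to take part should have one form and one place in the sequence of trial procedures. Here the form is either implied or signed, and the trigger is either a questionnaire or a signature. The information given beforehand is either an introductory briefing or a full account of the treatment protocol. A site that follows 2.1 could enter a patient without any signature. A site that follows 2.3 would obtain the signature, but only once the baseline examination was over.

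Participant protection is at stake. Patients could perform study-specific tests before they have had the full explanation and signed the form that the protocol itself requires. The record is also affected: with two rules on the page, neither a monitor nor a reader of the final report could say whether a given patient was consented according to protocol.

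**Working it through.** No figure is stated and no formula applies. The check sets the sections side by side.

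| Feature | Section 2.1 | Section 2.3 |
|---|---|---|
| What is consented to | Taking part in the study | Taking part in the study, and publication of results |
| Form | Implied | Written and signed |
| Trigger | Accepting a questionnaire | Signing the form |
| Information beforehand | Introductory briefing | Full explanation of the treatment protocol |
| Timing against baseline | Not stated | After the baseline examination |
| Timing against randomisation | Not stated | Not stated |

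1. **Same object.** Both sections speak of consent to participate in this study. Section 2.1 does not limit itself to the questionnaire, so the two rules overlap and differ on form, trigger and information.

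2. **Can both hold?** If the implied consent in 2.1 is enough for participation, the signature in 2.3 is redundant for that purpose. If it is not enough, whatever is collected before the signature precedes the consent that 2.3 requires. A two-stage process would resolve this, but the article describes none.

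3. **Order within 2.3.** The stated order is baseline examination, then explanation and signature. This comes from 2.3 alone, because 2.1 does not date its questionnaire against the baseline examination.

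4. **Is baseline trial data?** Section 2.6 compares baseline with posttreatment scores. It does not name the measures, but the only outcomes in 2.5 are pulmonary function and respiratory muscle strength. Baseline spirometry, MIP and MEP are therefore most naturally read as part of the baseline examination. Section 2.5 describes these as maximal manoeuvres, each performed three times. This step is an inference, since no section lists what the baseline examination contains.

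5. **Randomisation.** Section 2.3 says that the list is produced before the study starts, but not when an individual patient is assigned. Its sentence on assignment stands before its sentence on consent. Its sentence on enrolment also comes after the one on assignment, so the paragraph is not in time order and its sequence of sentences proves nothing about the sequence of events.

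6. **Extent.** Section 2.3 applies its rule to all patients and 2.1 makes no exception, so the conflict covers all 120 planned subjects.

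**The case against.** The best reply is that consent may be staged: briefing and agreement at the questionnaire, then full explanation and signature before treatment. An ethics committee approved the project. Section 2.1 undercuts this reading by speaking of consent to the study as a whole, but does not exclude it. It is also fair to say that spirometry may be routine for these patients, so that part of the baseline examination may not be study-specific. Both points limit how strongly the consequence can be put. Neither removes the conflict, because a staged process has to be written down and the article instead gives two unreconciled rules.

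A reader might infer more than the article supports:

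- **That testing precedes any valid consent.** This assumes that the consent described in 2.1 does not count, and that baseline data could be unusable as a result. Both judgements rest on norms outside the document. The supported statement is that the tests appear to precede the full explanation and signature. Nor does this follow from both rules, since 2.1 has no written consent and no stated baseline timing.
- **That the patients tested are acutely ill.** Section 2.2 requires symptoms of exacerbation, but the Introduction describes patients in stable condition. The article conflicts on this, and the consent point does not need it.
- **That consent follows allocation, so refusals could differ by arm.** Only sentence order suggests this, in a paragraph that is not chronological. Section 2.3 also says that patients will not know their group or the treatment they will be offered. That blinding may fail once tape is applied, but this does not explain arm-specific refusal at a signature given before treatment. No refusal rate or allocation ratio is stated, so any count of patients lost from one arm would be invented.

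**Conclusion.** The point stands as an internal contradiction with a participant-protection consequence. That 2.1 and 2.3 conflict on the form of consent, and that 2.3 puts the full explanation and signature after the baseline examination, is explicit and can be held with high confidence. That study measurements therefore come before the signature is a reasonable inference. It rests on the baseline examination including the outcome measures analysed in 2.6, and on at least some of these not being routine care.

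No numerical effect on the trial result can be derived, and no bias in the treatment comparison is shown. The reason to correct the text is that staff cannot follow both rules, and that 2.3 as written does not secure full explanation and signature before study-specific testing.

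**What to change.** In 2.1, delete the sentence on implied consent, or limit it expressly to completing the questionnaire. In 2.3, state one order:

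1. full explanation and signed written consent;
2. study-specific baseline measurements;
3. randomisation;
4. treatment.

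Say which baseline values, if any, come from routine care, so that it is clear which measurements must wait for the signature. Add that no patient is randomised before consent and baseline are complete.

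The cost is a wording amendment and a notification to the ethics committee. It adds no patients, procedures or measurements; the explanation and signature simply move ahead of the baseline examination.
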